##### Additional process measures

Behavioural regulations will be measured using the third version of the Behavioural Regulation in Exercise Questionnaire (BREQ-3). This BREQ questionnaire categorises physical activity behavioural regulation into external, introjected, identified, integrated, and intrinsic regulation plus amotivation, and has shown good factorial validity and reliability (111–114). The Cronbach's coefficient alpha (α) for the BREQ-2 subscales range between from 0.73 to 0.86 (112) and 0.86 for the additional integrated regulation subscale included in the BREQ-3 (115).

In addition to the BREQ-3, the Exercise Causality Orientation Scale (ECOS) will be an additional process measure (included at baseline only). Although the influence of exercise causality orientations has been widely under-researched, one study showed a positive association between autonomy orientation and both positive affect and more self-determined types of behavioural regulation (116). Therefore, the ECOS will be included as a process measure to provide information regarding the influence of exercise causality orientation on exercise choices, other psychological processes and outcomes. The ECOS has demonstrated good factorial and convergent validity, internal consistancy (Crobach's alphas 0.59–0.77) and test-retest reliability (ICCs 0.71–0.77) (117).

##### Evaluation of program performance, change and performance objectives

Specific questions addressing each of the change and performance objectives (developed as a part of the Intervention Mapping process) will be included in the post-program survey to evaluate the perceived impact of the program on these objectives. A general evaluation of the program will be undertaken using semi-structured individual interviews with program participants and implementing staff within the organisation. Individual interviews will be undertaken using an emergent-systematic approach to obtain detailed information about the perceived effectiveness, strengths and limitations of the program and its implementation.

#### Data processing and analysis

This project will use a variety of analytical methods, applying qualitative and quantitative techniques. The process evaluation will compare descriptive statistics of the sample population and groups within the sample to de-identified data from the support and care worker population from all participating sites and areas. Fidelity recordings of the sub-sample of initial interviews will be scored by members of the research team who are not responsible for undertaking initial interviews using a customised fidelity checklist. An overall score for each recording will be calculated as a proportion of the highest possible score, and descriptive statistics will be used to present overall fidelity of the initial interview sub-sample. Mean scores will be calculated for individual items on the HCCQ (inversing the score for item 13) to produce a mean score of overall autonomy support. Per protocol analysis will be undertaken using a random effects mixed-model to compare baseline, 3 month and 9 month time points for all well-being and behavioural outcome measures. Accelerometer data will be processed using the cut-points outlined by Esliger, Rowlands (100) to determine total minutes of sedentary, light, moderate and vigorous activity for each 7 day period of continuous accelerometry. Domain-specific means will be calculated for the PNSE and BREQ-3 and these will be analysed for differences in well-being or behavioural outcomes and movement between domains (i.e., movement toward more-self-determined types of motivation and increases in perceived support of psychological needs). Qualitative interviews undertaken with program participants and implementation staff will be audio recorded and transcribed. The transcripts will be coded by two independent researchers, and analysed using a structured thematic approach as described by Braun and Clarke (118). Conflicts will be resolved through discussion between the two researchers. A third researcher will be consulted in situations where conflicts cannot be resolved.

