### Intervention mapping step 4: producing program components and materials—the activity for well-being program

As a result of the first three Intervention Mapping steps, the final program components were developed and are outlined here: Participants will undertake an initial need-supportive interview with an Exercise Physiologist (addressing six of 12 change objectives). The Motivational Interviewing-inspired interview will be undertaken using an empathetic and autonomy supportive approach and will use collaboration with the participant to develop an individualised activity plan and promote motivation for change (91, 92). During the course of the interview, the Exercise Physiologist will collaborate with the participant to develop an individualised and realistic physical activity plan that provides participant choice for activity. The participants will be encouraged to incorporate friends and family into individual activity plans to support environmental and social support outside of the participant-practitioner interactions. The Exercise Physiologist will provide a supporting role and may assist the participant to identify activities within the community (i.e., dance or exercise classes, social sporting groups) that he or she may want to participate in, develop a home, gym or walking program, and provide any other motivational, or technical support that the participant feels that he or she needs. The interview will be also used to obtain information regarding participant goals, exercise history and barriers to activity to guide this process. During this initial appointment the Exercise Physiologist will also educate the participant on goal-setting, action, and coping planning, and using affect, RPE and self-pacing for activity intensity (four of 12 change objectives). Each participant will have previous exposure to the use of Borg's RPE scale (22) and Hardy and Rajeski's Feeling Scale (16) while undertaking a 6 min walk during baseline testing.

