### Intervention mapping step 5: planning program adoption and implementation

#### Participants and research design

Participants will be self-selected from the population of frontline aged care workers, employed by the funding organisation. All participants will be recruited from the Adelaide metropolitan area and Fleurieu Peninsula, South Australia. Employees will be recruited via a generic email that will be sent out to all community-based support workers and care workers from participating residential sites. Expressions of interest will also be obtained through flyer drops and active promotion of the program at team meetings. This project will be undertaken using a mixed methods research design including a single-cohort, pre-post feasibility study, followed by a thorough process evaluation and qualitative evaluation of the program. Prior to commencing baseline testing, the researchers will obtain informed consent from each participant. Baseline testing will begin during the Australian late spring—early summer period and will be undertaken using a rolling recruitment until a sufficient number of participants have been enrolled in the program (~20–30 participants). Participants will complete a demographic questionnaire and undertake a pre-exercise screen using the Adult Pre-exercise Screening System (APSS) (97). The APSS is the Australian standard pre-exercise screening system that was developed as a collaboration between Exercise and Sports Science Australia, Fitness Australia and Sports Medicine Australia. Any participants who indicate previously diagnosed conditions, or signs/symptoms of cardiovascular disease in the first stage of the APSS will be required to obtain a medical clearance prior to undertaking exercise testing or program commencement. Participants will be included if they are 18 years of age or older, able to speak fluent English, currently employed as a frontline worker at the funding organisation and able to engage in moderate physical activity as defined by the American College of Sports Medicine (98). Ability to speak fluent English was placed as an inclusion criterion as many measures that will be used within this study are questionnaire-based and the lack of an ability to speak fluent English may impact the validity of these measures. Participants will receive an honorarium for undertaking the post-intervention and follow-up measures (a $25 and $50 gift card for these time-points, respectively). The honorarium will not be impacted by adherence to the intervention; these will be given for undertaking the measures only. As this is a feasibility study, sustainability of the program at an organisational level will not be addressed within the scope of this project; however, at an individual level the program was developed to promote long-term maintenance of behaviour change.

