#### Evaluation of impact and outcomes

##### Behavioural outcome objectives—physical activity behavior

The behavioural outcome objectives for the Activity for Well-being project are to increase physical activity behaviour at 3 months and to maintain potential increases at 9 months post-intervention. Physical activity behaviour will be objectively measured using 7 day continuous accelerometry (GENEactiv, UK) at three time points (baseline, 3 months and 9 months). Two-day physical activity recall using the adult version of the Multimedia Activity Recall for Children and Adolescents (MARCA, Aus) will be used to assess changes in activity patterns and use of time between the three time points.

Esliger, Rowlands (100) demonstrated good validity (*r* = 0.97, *p* < 0.001), and intra- and inter-test reliability (Coefficient of Variation 1.8 and 2.4%, respectively) of GENEactiv accelerometers as measured using an Instron Multi-Axis Shaking Table. The authors also demonstrated that these accelerometers are comparable to portable gas analysis for measuring Metabolic Equivalents (METs) of activity achieving an area under the receiver operating characteristic curve (AUC) of 0.98, 0.91, and 0.91 during sedentary, moderate and vigorous, respectively, and high sensitivity and specificity for these activity categories (72–98%). The adult MARCA software has demonstrated good convergent validity for measuring physical activity levels (METs) compared to accelerometry, with Spearman coefficients (rho) at 0.72 (0.49–0.86), and very high test-retest reliability with intra-class correlation coefficients (ICCs) ranging from 0.99 to 1.00 (101).

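### The only stated outcome analysis is per protocol, left undefined; on the usual meaning it would be expected to overstate the change in physical activity, by an amount the article does not allow one to fix

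*Protocol article*

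**What the plan says.** Data processing and analysis gives one inferential analysis of outcomes: "Per protocol analysis will be undertaken using a random effects mixed-model to compare baseline, 3 month and 9 month time points", and applies it "for all well-being and behavioural outcome measures". Neither that section nor any other defines per protocol, sets an adherence threshold, or adds an analysis of everyone enrolled, even as a sensitivity analysis.

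The surrounding design matters here:

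- Participants and research design describes a "single-cohort, pre-post feasibility study, followed by a thorough process evaluation and qualitative evaluation of the program", with recruitment continuing "until a sufficient number of participants have been enrolled in the program (~20–30 participants").
- In the program components section (step 4), the exercise physiologist and participant together "develop an individualised and realistic physical activity plan that provides participant choice for activity". There is no fixed dose.
- The behavioural objective is "to increase physical activity behaviour at 3 months and to maintain potential increases at 9 months post-intervention". On measurement: "Physical activity behaviour will be objectively measured using 7 day continuous accelerometry (GENEactiv, UK) at three time points".
- On payment for follow-up measures, Participants and research design says: "The honorarium will not be impacted by adherence to the intervention; these will be given for undertaking the measures only".
- Dose delivered and dose received says that logs of support, communications and website engagement will be kept. Dose received is scored from self-reported frequency of use in the post-program survey.

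**The concern.** The intervention is a self-chosen activity plan and the behavioural outcome is physical activity. A set restricted to people who followed their plan would therefore be selected on something close to the outcome. With no control group, no comparator undergoes the same selection, so any distortion passes directly into the pre-post change.

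The restriction also has no technical purpose. A random-effects mixed model can already use every participant with at least some data, and at 20 to 30 people each exclusion costs precision.

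At stake is whether the reported change describes the workers who enrolled or only those who took to the program. The Discussion says a positive impact may support a change in clinical practice, and it recommends a fully powered randomised trial. For both uses the change among all enrolled workers is the natural quantity.

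**Working it through.** **Nothing to reproduce.** The article gives no alpha, power, effect size, SD or dropout rate. The 20 to 30 is a recruitment target without a calculation.

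**Inputs.** From the article: N = 20 to 30, single cohort, per-protocol set. Assumed, because the article gives neither: the excluded share q (20–40%) and the correlation ρ between adherence and change in the outcome (0, 0.3, 0.5).

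**Bias.** Let adherence be standard normal, and let change be measured in SDs with true mean zero. If the least adherent share q is left out, the mean change among those kept is

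bias = ρ × φ(z_q) / (1 − q),

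where z_q is the normal quantile at q and φ the normal density. For q = 0.30, z_q = −0.524 and φ = 0.348, so φ/(1 − q) = 0.348/0.70 = 0.497. The bias is then 0.3 × 0.497 = 0.149 SD, or 0.5 × 0.497 = 0.248 SD.

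**Chance of a false increase.** This was simulated with 20,000 runs per setting and true mean change zero. The test was a paired t-test at two-sided 5%, counting only significant increases, for which the nominal rate is 2.5%.

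| Excluded | ρ | Bias (SD of change) | False increase, N = 20 (analysed) | False increase, N = 30 (analysed) |
|---|---|---|---|---|
| 20% | 0 | 0 | 2.2% (16) | 2.4% (24) |
| 20% | 0.3 | 0.105 | 5.8% (16) | 7.0% (24) |
| 20% | 0.5 | 0.175 | 10.3% (16) | 13.7% (24) |
| 30% | 0 | 0 | 2.5% (14) | 2.3% (21) |
| 30% | 0.3 | 0.149 | 7.7% (14) | 9.8% (21) |
| 30% | 0.5 | 0.248 | 15.1% (14) | 20.9% (21) |
| 40% | 0 | 0 | 2.5% (12) | 2.6% (18) |
| 40% | 0.3 | 0.193 | 8.9% (12) | 12.1% (18) |
| 40% | 0.5 | 0.322 | 19.0% (12) | 28.3% (18) |

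With everyone analysed, the rate stayed at 2.2–2.7% in every setting.

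**Precision.** The 95% half-width for a mean change is t(0.975, n − 1)/√n, in SDs, taking the SD as unchanged. Going from 20 to 14 people: 2.093/√20 = 0.47, rising to 2.160/√14 = 0.58. Going from 30 to 21: 2.045/√30 = 0.37, rising to 2.086/√21 = 0.46.

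**Limits of this check.** It models exclusion of people who were measured but did not adhere, and it uses a paired test rather than the planned three-time-point model. The zero bias with everyone analysed assumes that the excluded people have follow-up data.

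**The case against.** The strongest reply is that the exclusion is inferred. The article never says who is left out, and an article may leave the definition of an analysis set to a fuller document. Three readings are open:

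- **Adherers only.** This is the usual meaning and the one calculated above.
- **Completers.** Selection is then on retention. People who leave have no later measurements, so an all-enrolled model adds mainly their baselines and any 3-month data. It reduces the selection only if data are missing at random.
- **Recipients of the program.** The initial interview and support contacts are logged, and a set defined on them is less tied to activity done.

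A reader might infer that the plan is known to discard non-adherers' data, and that the payment rule proves it. It does not. Paying for measures regardless of adherence shows an intention to measure everyone, and it is equally consistent with analysing everyone measured. It does show that, on the adherers-only reading, data would be left out that the study had sought.

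The size is also open to challenge. Neither the exclusion rates nor the correlations come from the article, and the argument is weaker for the K-10 and AQoL-8D, which are further from adherence than activity is. The study is a feasibility study with no stated decision rule, so the false-increase rates drive no stated decision. The Discussion already concedes low power, the lack of a control group and seasonal confounding, and the process evaluation would show low engagement.

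All of this stands, and it limits the claim and its severity. It does not remove the point: the article names its analysis population, names only this one, and its acknowledged limitations do not include selection by that population.

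**Conclusion.** The point holds in a qualified form. A per-protocol mixed model, undefined, is the only stated analysis of the well-being and behavioural outcomes. If it means adherers only, the change in physical activity would be expected to be overstated relative to all enrolled workers whenever adherence and change are positively correlated. That is plausible when the intervention is itself an activity plan.

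The overstatement is roughly 0.1 to 0.3 SD of change under assumed exclusion of 20–40% and correlation of 0.3–0.5, and nil at zero correlation. The article does not fix the amount. A reader might go further and conclude that the estimate is definitely biased upward, or that it could not inform a later trial. The documents support neither, because the set is undefined and the correlation unknown. Given the feasibility aim, the severity is moderate.

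**What to change.** In Data processing and analysis, make the main analysis the same mixed model fitted to all enrolled participants with a baseline measure. It should use all available 3- and 9-month data regardless of adherence, with the missing-at-random assumption stated.

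Keep per protocol as a labelled supportive analysis. Define it in advance from the contact and program-use logs already planned, rather than from activity done, and report the number excluded.

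The cost is a short edit to the analysis section, with no new data. The estimated change may look smaller. If the sponsor meant completers, the edit helps only as far as missing at random is credible.

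### The accelerometer outcome is fixed as unscaled 7-day totals, so unequal wear between time points would read as a change in activity; minutes per valid day would avoid this

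*Protocol article*

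**What the plan says.** The behavioural aim is to "increase physical activity behaviour at 3 months and to maintain potential increases at 9 months post-intervention". The article's section on the behavioural outcome objectives gives the measure: "Physical activity behaviour will be objectively measured using 7 day continuous accelerometry (GENEactiv, UK) at three time points".

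The Data processing and analysis section gives the scoring. It begins "Accelerometer data will be processed using the cut-points outlined by" a published validation study, and states the purpose as "to determine total minutes of sedentary, light, moderate and vigorous activity for each 7 day period of continuous accelerometry". That sentence fixes the statistic (a total), the classes (four) and the period (seven days).

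The same section gives the comparison: "Per protocol analysis will be undertaken using a random effects mixed-model to compare baseline, 3 month and 9 month time points". It states no wear-time term and no conversion to a daily rate. The sample is small and has no comparison group; recruitment continues "until a sufficient number of participants have been enrolled in the program (~20–30 participants").

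**The concern.** A sum over a recording measures two things at once: how active the person was and how much of the week was captured. The two separate cleanly only if every recording is complete. If a participant wears the device for seven days at one visit and six at another, the difference between the two sums contains a wear component that the model, as described, attributes to time.

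The design makes this hard to detect. It follows one group before and after the programme, so no comparison arm shows whether wear shifted. The incentive to complete measures also differs across the time points being compared: the Participants and research design section offers a $25 gift card after the intervention and $50 at follow-up, and mentions none at baseline. That could make wear better or worse at later visits. The documents do not indicate which, so the bias could produce a false gain or a false relapse.

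A second issue is conditional. Only four classes are named, and none is for sleep or off-body time. If low-movement periods are not removed before the cut-points are applied, they can only enter the sedentary class.

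**Working it through.** The plan states no accelerometer total, target difference or power figure, so there is nothing of its own to reproduce. The inputs are the seven-day period and the four classes from the article. Behavioural values below are assumptions and are marked as such.

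**1. Recording window.** Read as 24 hours a day: 7 × 1,440 = 10,080 min.

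**2. Effect of lost recording time on an activity total.** If *d* days are captured and the lost time is typical of the week, the proportional change in the total is *d*/7 − 1. With an assumed constant 60 min/day of moderate-to-vigorous activity:

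| Days captured | Total (min) | Change in total | Mean per captured day (min) |
|---|---|---|---|
| 7 | 420 | 0 | 60 |
| 6.5 | 390 | −7.1% | 60 |
| 6 | 360 | −14.3% | 60 |
| 5 | 300 | −28.6% | 60 |
| 4 | 240 | −42.9% | 60 |

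The percentages do not depend on the assumed 60 min/day. The daily mean does not move.

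**3. True gain that one lost day could hide in one person.** Suppose seven days are captured at baseline and six at follow-up. The totals are equal when 6 × follow-up rate = 7 × baseline rate, so the hidden gain is (7/6 − 1) × baseline rate. This is 10 min/day at an assumed baseline of 60, 5 at 30 and 15 at 90.

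**4. Effect on the group mean.** If a share *p* of participants lose one day at one time point only, the mean total shifts by *p* × (minutes per day). With an assumed 20% and 60 min/day this is 0.20 × 60 = 12 min on 420, or 2.9%. The full 14.3% would need every participant to lose a day at one visit and none at the other.

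**5. Sleep, if it is not removed.** Sleep minutes per week are 7 × hours × 60. At an assumed 7 h this is 2,940 min (2,940/10,080 = 29.2%); at 8 h it is 3,360 min (33.3%). With an assumed 6–10 h/day of waking sedentary time, the sedentary total becomes (waking + sleep)/waking times the waking value, from (10 + 7)/10 = 1.7 to (6 + 8)/6 = 2.3.

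**6. Direction for the sedentary class.** Late fitting or a flat battery leaves no data, so the sedentary total falls with the others. Recorded off-body time that is not screened out does the reverse: a full day adds up to 1,440 sedentary minutes gross, before subtracting the sedentary minutes that day would have had anyway.

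**The case against.** The strongest reply is that this is a journal article. Sleep scoring, non-wear detection and valid-day rules are normally left to a full protocol or analysis plan, which is not shown. The text does not say that sleep or off-body time is scored as sedentary, nor that cut-points run on unscreened data. This stands. A reader might infer from the four named classes that sleep and non-wear are counted as sedentary, but listing the reported classes does not describe the pre-processing, so that part can only be put conditionally. Even then it concerns the sedentary total. Moderate and vigorous minutes, which bear most directly on the aim of increasing activity, would be largely unaffected, and a stable sleep duration would largely cancel in a within-person comparison.

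It is also fair that a total over seven complete days is simply seven times the daily mean, so the two scales agree when wear is complete. A claim that every total varies with wear would be too strong. However, no restriction to complete recordings is stated, and imposing one in a sample this small would discard scarce data, possibly not at random.

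Finally, the two-day recall "will be used to assess changes in activity patterns and use of time between the three time points", which gives a second view of time use. It is not linked to the accelerometer scoring and does not correct it.

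What survives is the stated choice of an unscaled total. That is written down, not left out.

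**Conclusion.** The point holds for the metric. As written, the activity outcome falls by one seventh (14.3%) for each lost day of wear with no change in behaviour, and differences in wear between time points would be taken as change over time. The percentages assume that the lost time is typical of the participant's week; off-body time confined to sleep would not lower the activity totals. The effect on the group mean depends on how many participants lose wear at one visit and not another, which the documents do not give.

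The inflation of sedentary time (29–33% of the week at an assumed 7–8 h of sleep) applies only if sleep is left in.

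Two stronger readings are not supported. One is that compliance will fall at later visits and mimic relapse at 9 months: nothing in the documents says so, and the rising gift-card value could work the other way. The other is to set one person's loss (300/7 = 43 min at an assumed 300 moderate min/week) against the 26 min/week difference in the walking pilot described in the Introduction. That compares an individual's assumed loss with a between-group difference, which the article itself lists among non-significant trends.

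Severity is moderate to low. This is a feasibility study of about 20–30 people, and its Discussion already warns of low power and of limited conclusions without a control group.

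**What to change.** Define the accelerometer outcome as mean minutes per valid day in each intensity class, in place of the seven-day total. State the minimum number of valid days for a recording to count, and keep recordings shorter than seven days in the mixed model on the per-day scale. State that the cut-points are applied to waking wear time only, after sleep and off-body time have been identified and removed. Reporting the number of valid days at each time point would let readers see whether wear differed.

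The cost is a standard processing step and a change of wording, which can be made before analysis. A few recordings may fall below the validity threshold. A daily mean still assumes that lost days resemble worn ones, which may be imperfect in a workforce that includes shift workers, but it removes the direct dependence on the number of days captured.
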